## Abstract

**Background:**

Cystic fibrosis (CF) is an autosomal recessive disorder caused by abnormal function of the chloride ion channels and characterized by pancreatic insufficiency and chronic endobronchial airway infection. Pulmonary dysfunction is very common and could lead to a reduction in the quality of life. Airway clearance techniques (ACT) and physical exercises are introduced as one of the main components of treatment. Therefore, it will be of interest to examine the effect of aerobic exercises compared to conventional chest physiotherapy (CPT) on pulmonary function, functional capacity, sputum culture, and quality of life in patients with CF.

**Methods:**

Thirty patients with CF will participate in a double-blind parallel controlled trial containing 18 sessions of treatment. Group A consists of CPT and placebo aerobic exercise, and group B includes aerobic exercise and placebo CPT. Pulmonary function, functional capacity, sputum culture, and quality of life will be evaluated with a spirometry test, 6-min walk test (6MWT), sputum culture test, and the Cystic Fibrosis Questionnaire-Revised (CFQ-R), respectively, before and after the intervention.

**Discussion:**

We will evaluate and compare the effectiveness of aerobic exercises and conventional chest physiotherapy on pulmonary function, functional capacity, sputum culture, and quality of life. Comparing these two treatment patterns can contribute to a better understanding of the effectiveness. Therefore, if there is a significant difference between the two treatments, the superior treatment will be prioritized clinically.

**Trial registration:**

https://www.irct.ir, IRCT20210505051181N5. Registered on 19 February 2023.

**Supplementary Information:**

The online version contains supplementary material available at 10.1186/s13063-023-07719-w.

## Introduction

### Background and rationale {6a and 6b}

Cystic fibrosis (CF) is one of the most common autosomal recessive diseases [1]. Pulmonary complications of CF are one of the most common causes of death with 60% mortality, especially in children and adolescents [1, 2]. Despite the lower prevalence of this disease in the Asian continent (1 per 35,000 births), the number of patients has been increasing over the last two decades [1]. The CF affects various systems with more involvement in the respiratory system, causing very viscous, hard, and sticky mucous secretions that accumulate in the excretory pathways [1]. This is the basis for inflammation, recurrent infections, and tissue fibrosis [3, 4]. With every episode of pulmonary infection, a high percentage of a patient’s lung function is irreversibly lost [4]. As a result, the quality of life is reduced and can be very disruptive in daily activities [1–3, 5]. Therefore, choosing the appropriate treatment is important in treating these patients and reducing the disease burden [3, 6]. Airway clearance techniques (ACT) and physical exercise are introduced as one of the main components of treatment [1, 3, 7, 8].

Conventional chest physiotherapy (CPT) is the oldest form of ACT that was introduced in the 1940s [9] and is recommended as the standard treatment that can be performed by all people of all ages [10]. Based on the results of most studies, including guidelines and systematic reviews, there is no meaningful difference between different ACTs (including CPT, active cycle of breathing technique (ACBT), autogenic drainage (AD), and oscillating positive expiratory pressure (OPEP) devices). They all lead to more clearance of the produced sputum, reducing the recurrence of pulmonary infections and slowing down the progression of lung destruction. This in turn improves lung function and increases the quality of life for patients [3, 7, 8, 11–16]. Choosing the best method depends on the patient’s ability to perform, preference, and available facilities [7].

Aerobic exercises are another important treatment option, as they increase endurance and cardiopulmonary fitness, aerobic capacity, mental health, and quality of life [17–19]. In addition, it is hypothesized that due to the increase in the respiratory rate and volumes and more passage of substances across the respiratory membranes and resultant increased ventilation, this treatment can also have significant effects on the evacuation of secretions [9, 20–23]. In addition to softening and moistening respiratory secretions, it also increases cough stimulation in patients and has been very effective in draining respiratory mucus [18, 20, 23, 24]. Limited studies also demonstrate its positive effects on respiratory infections [25, 26].

CPT is still the standard and most widely used method for children and adolescents with CF, because teaching other ACT methods has proven to be difficult for them to follow, and their effectiveness depends on correct learning and implementation processes. However, due to the inconvenience, time-consumption, and dependence of CPT on others, nowadays it is not uncommon, for most patients and even their families to prefer the alternative methods [7]. Also, aerobic exercise is a readily available activity that is practicable and clinically recommended [20].

Several studies have investigated the effectiveness and quality of the implementation of unsupervised interventions at home by patients or their parents [9, 29, 30], with results demonstrating that treatment adherence is 30% [9]. Study results reveal that unsupervised treatment has fewer positive effects compared with supervised treatment [25, 31, 32]. Numerous studies, including systematic reviews (alluding to the controversy in the results of aerobic exercises and the low methodological quality of these studies), have mentioned the need for further investigation in this field so that it can be credible to recommend the possibility of using aerobic exercises as a viable alternative and independent ACT [17, 20, 33–35].

To the best of the authors’ knowledge, a study comparing aerobic exercise with CPT with high-quality and precise design has not yet been investigated. Therefore, this study aims to compare the effect of aerobic exercises compared to CPT on pulmonary function, functional capacity, sputum culture, and quality of life in patients with CF. This is so that if significant changes are observed due to aerobic exercises compared to CPT, clinically, aerobic exercises can be recommended among treatment priorities.

### Objectives and hypotheses {7}

In this trial, we aim to include 30 children and adolescents of CF patients into a 1:1 randomized controlled trial study. We will compare the effects of conventional chest physiotherapy (CPT) and sham aerobic exercise in one group and aerobic exercise and sham CPT in the other group. The primary objective is to evaluate the effects of the 18-session aforementioned treatments on pulmonary function (FEV1) and functional capacity in children and adolescents with CF. The secondary objective is to assess the changes in sputum culture, pulmonary function (FVC), and quality of life of CF patients.

We hypothesize that there will be an increase by at least 7.1% in FEV1% percent predicted (minimally clinical important difference (MCID) considered for FEV1 [36]), a significant increase in the amount of FVC, at least 33-m increase in the distance covered in 6MWT (MCID considered for 6MWT [36]), a significant increase in the percentage of negative sputum culture tests and reduction of colony count tests after 6 weeks of aerobic exercise and CPT in CF patients, and a significant difference between the two groups. Also, the CFQ-R quality of life questionnaire score is expected to have a significant increase of at least 11.4 points in the physical domain, 7.3 points in the respiratory domain (MCIDs considered for CFQ-R [36]), and in the overall score.

### Trial design {8}

The current project is a double-blind 1:1 randomized controlled trial study designed to investigate and compare the effects of aerobic exercises and CPT in two parallel groups: group A consisting of CPT plus sham aerobic exercise and group B consisting of aerobic exercise and sham CPT. This study will be conducted at the CF specialized clinic of the Children’s Medical Center Hospital, Tehran, Iran; children and adolescents with confirmed diagnoses of CF will be randomly allocated to either group A or B.

Primary data points including FEV1, 6MWT, and secondary outcomes including sputum culture test (key secondary), FVC, and CFQ-R quality of life questionnaire will be assessed before and after treatments. It is expected that both treatments will have meaningful effects on the aforementioned variables and if significant changes are observed due to aerobic exercises compared to CPT, clinically, aerobic exercises will be recommended among treatment priorities.

## Methods: participants, interventions, and outcomes

### Study setting {9}

Data will be collected at the CF specialized clinic of the Children’s Medical Center Hospital, Tehran, Iran. Patients diagnosed with CF will be referred by a pediatric pulmonologist ([name]) or called among the previous files available.

### Eligibility criteria {10}

Table 1 summarizes the inclusion and exclusion criteria for the groups. Participants must meet all the eligibility criteria to be included.

**Table 1 Tab1:** Inclusion and Exclusion criteria of the study

Inclusion criteria	Exclusion criteria
1- Confirmed diagnosis of cystic fibrosis based on positive sweat test or genetics test by a specialist doctor	1- Active hemoptysis, pneumothorax, hemodynamic instability, severe hypoxia, acute airway infection, and cognitive disorders
2- Age 6 to 18 years	2- Having cardiac disease such as heart failure or arrhythmia, neurologic and orthopedic disorders, or chest trauma
	3- History of fever, IV antibiotics, or hospitalization in the last 1 month
	4- Having severe uncontrolled gastroesophageal reflux
	5- Severe lung disease (FEV1% < 30%)
	6- Lung transplantation or on the waiting list
	7- Requirement of additional oxygen with exercise
	8- Having uncontrolled diabetics
	9- Improper patient cooperation during treatment sessions
	10- Absence in 3 or more consecutive sessions

The age range considered for inclusion criteria is 6–18. Based on the review and study of patient archives and registrations in the center, most of the patients who are referred to the CF specialized clinic are between the ages of 6 and 18, and this age range is the most accessible. In addition, those who are outpatients mostly have the same stage of chest disease; otherwise, patients with higher and more acute stages of chest disease are hospitalized and those with better conditions and in milder stages usually do not have routine clinical visits and are referred only for check-ups. Thus, participants will be among patients with more similar conditions.

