### Interventions {11a}

The treatment session will commence 30 min after the first examination. Group A will first include the main treatment of CPT and then a placebo of aerobic exercise; group B will first include the main treatment of aerobic exercise and then a placebo of CPT (the inverse of Group A). The study will be conducted over 6 weeks, 3 times a week, with a total of 18 sessions. Make-up sessions will be allowed if a session is missed. The duration of the entire treatment session will last approximately 70 min.

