### Allocation concealment {16b}

The randomization process was done by a statistician ([name]) before the start of the study. After the initial evaluation of participants by the examiner, who has enough experience and knowledge to do it, sealed numbered envelopes, corresponding to the sequential number of each person entered into the study, will be presented and the therapeutic intervention will be adjusted based on the letters inside the envelopes. The examiner and participants will be unaware of the letters inside the envelopes until the end of the study.

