### Plans to promote participant retention and complete follow-up {18b}

Participant retention and complete follow-up are promoted by the monitoring of the physical therapist. In case of withdrawal of patients from the study, their data will be counted as drop-outs.

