### Methods in analysis to handle protocol non-adherence and any statistical methods to handle missing data {20c}

In order to increase adherence, patients will be contacted weekly and given gifts like toys, edibles, and accessories for more encouragement and cooperation. Treatment will be done in a well-designed room and accompanied by music. Missing data will be disposed of with the Multiple Imputation (MI) method.

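### Exclusion criteria 9 and 10 can be met only after allocation, so as written they exclude randomised children for behaviour during treatment, and the plan does not say whether those children are followed up or analysed.

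*Protocol article*

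**What the plan says.** All references are to the protocol article.

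- **Eligibility criteria {10}, Table 1.** Exclusion criterion 9 is "Improper patient cooperation during treatment sessions" and criterion 10 is "Absence in 3 or more consecutive sessions". The text above the table gives the list its force: "Participants must meet all the eligibility criteria to be included".
- **Allocation concealment {16b}.** After the initial evaluation, numbered envelopes "corresponding to the sequential number of each person entered into the study, will be presented and the therapeutic intervention will be adjusted" according to the letter inside.
- **Interventions {11a}.** "The treatment session will commence 30 min after the first examination". There are three sessions a week for six weeks, 18 in all, and "Make-up sessions will be allowed if a session is missed".
- **Relevant concomitant care {11d}.** The only activity before treatment is a breathing technique taught for home use. It is not a supervised run-in.
- **Outcomes {12}.** Measurements are taken at baseline and after 6 weeks only.
- **Sample size {14}.** An earlier trial had 11 per group. A 30% drop-out allowance brings this to 15 per arm.
- **Retention {18b}.** "In case of withdrawal of patients from the study, their data will be counted as drop-outs".
- **Non-adherence and missing data {20c}.** "Missing data will be disposed of with the Multiple Imputation (MI) method".

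**The concern.** An eligibility criterion should be decidable before allocation. These two are not: they describe how a child behaves in sessions that the allocation has already determined. Applied as exclusions, they take randomised children out on the basis of something the assigned treatment may have influenced.

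The arms differ in what they ask of a child. Group B does progressive treadmill and bike work at set heart rates. Group A has manual treatment and then low-intensity motorised cycling. Different rates of poor cooperation or absence are therefore plausible. A link with outcome is plausible too: the Background says that each pulmonary infection costs lung function that is not regained, and one infection could account for a week of absence.

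With 15 children per arm, a handful of such removals can move the FEV1 or 6MWT comparison. The result is meant to inform which treatment takes clinical priority.

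**Working it through.** **1. Order of events.** The sequence is initial evaluation, envelope, first session, then behaviour and attendance in sessions. Criteria 9 and 10 belong to the last step, so no child can meet either before being randomised.

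**2. How little triggers criterion 10.** 3 absences ÷ 3 sessions per week = 1 week, and 3 ÷ 18 = 16.7% of the course.

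**3. The plan's own sample-size figure.** 11 × 1.30 = 14.3, rounded up to 15 per arm and 30 in total, which reproduces the stated figure. (Dividing instead, 11 ÷ 0.70 = 15.7, gives 16.) The margin is 15 − 11 = 4 children per arm. A 30% loss from 15 leaves 15 × 0.70 = 10.5. The allowance is thus sized for about 11 per arm with data, whereas multiple imputation would keep all 15 in the analysis.

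**4. What removal could do.** The documents give no rate of such removals and no link with outcome, so this is an illustration on assumed values. The set-up is 15 per arm, no true effect, outcome change with SD 1, a two-sided two-sample t-test at 0.05, and 40,000 simulated trials per scenario. Each child has a latent cooperation or attendance score with correlation ρ to the outcome change. The lowest scorers are removed.

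| Removed (one arm vs other) | Bias in SD at ρ = 0.3 / 0.5 / 0.8 | False-positive rate at ρ = 0.3 / 0.5 / 0.8 |
|---|---|---|
| 0 vs 0 | 0 / 0 / 0 | 4.9% / 5.0% / 4.9% |
| 2 vs 0 | 0.07 / 0.11 / 0.18 | 5.6% / 6.3% / 8.6% |
| 4 vs 1 | 0.09 / 0.15 / 0.24 | 5.6% / 7.4% / 11.5% |
| 4 vs 0 | 0.13 / 0.21 / 0.34 | 6.1% / 8.2% / 14.4% |
| 4 vs 4 | 0 / 0 / 0 | 5.2% / 5.7% / 7.6% |

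The bias should be proportional to ρ, and it is. For 4 vs 0, the unrounded values give 0.129 ÷ 0.3 = 0.43, 0.210 ÷ 0.5 = 0.42 and 0.338 ÷ 0.8 = 0.42.

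The last row matters: equal removal by the same mechanism leaves the difference unbiased. The false-positive rate there still rises somewhat at high ρ, because outcome-related trimming makes the t-test's standard error too small.

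**5. The handling rules side by side.** Table 1 excludes the child, {18b} labels withdrawals as drop-outs, {14} allows for their loss, and {20c} imputes missing data. None of these says whether a child meeting criterion 9 or 10 is still assessed at week 6, imputed, or analysed in the allocated arm. With only two time points, the children lacking a week-6 value would largely be those excluded or withdrawn. If they are removed, imputation has little left to do.

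**The case against.** The strongest reply is that several stronger readings go beyond the text. They do, and they should be set aside.

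- **That these children are deleted from the primary analysis.** A reader may infer this from the exclusion label, the drop-out sentence and the 30% allowance, but it is not stated. Counting as a drop-out can be a participant-flow label, and a drop-out allowance is common even where everyone is analysed.
- **That the drop-out sentence contradicts the imputation plan.** The two can be read together: the child drops out and the missing outcome is imputed. They are unreconciled, which is weaker than contradictory.
- **That make-up sessions contradict criterion 10.** Making up an isolated missed session can coexist with a rule about an unbroken run of three.
- **That an unblinded therapist decides who is removed, or that the children who deteriorate are the ones who go.** The protocol does not say who judges cooperation or why children are absent.
- **That the imputation would be too weak to help.** The imputation model is not described.
- **That the arms differ sharply in burden.** Both arms get a cycling component and a manual component in sessions of about 70 minutes. They differ in intensity, so the contrast is real but narrower than exercise against passive treatment.

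It can also be said that an article may leave the analysis population to a fuller document. That is fair for an omission, but this point concerns a rule the article states. If a child excluded under it is not assessed at week 6, no later analysis plan can recover the data.

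**Conclusion.** The point stands in this form. Two post-allocation events are listed as eligibility exclusions, so following Table 1 literally excludes randomised children for conduct during their assigned treatment. Nothing in the article keeps them in follow-up or in the analysis.

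Bias is conditional: removals must differ by arm and relate to outcome. Where they do, losing 2 to 4 of 15 children from one arm only, at ρ between 0.3 and 0.8, gives about 0.07 to 0.34 SD and a false-positive rate of about 5.6% to 14.4% against a nominal 5%. The top of that range needs both the largest one-sided loss and the strongest correlation. The counts and correlations are assumptions, and the simulation uses a t-test on change, not the planned baseline-adjusted ANCOVA. Equal removal by the same mechanism gives no bias.

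It would be too much to conclude that the randomised comparison is already broken. The documents show a rule that permits this, not that it will happen.

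**What to change.** 1. Take criteria 9 and 10 out of the eligibility list. Record both events as non-adherence, used only to define a per-protocol sensitivity set.
2. State that every randomised child is invited to the week-6 spirometry, 6MWT, sputum culture and CFQ-R, whatever the attendance or cooperation.
3. State that the primary ANCOVA includes all randomised children in their allocated arm.
4. Reword the drop-out sentence in {18b} to match, and use the multiple imputation in {20c} for week-6 outcomes that cannot be obtained.
5. The sponsor should reconcile whether these events also end a child's sessions, and how criterion 10 fits with make-up sessions. That is a treatment question, on which this point proposes no rule.

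The cost is a protocol amendment and a few extra week-6 visits. The effect estimate will include non-adherent children, a small downside that the per-protocol sensitivity analysis helps readers to judge.

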## Data collection and management

### Plans for assessment and collection of outcomes {18a}

Outcomes are assessed at two time points, at baseline, and after treatment sessions, by the blinded examiner who has enough experience and knowledge to do it. Also, the demographic data will be gathered by the examiner in the first session. The Persian version of the CFQ-R questionnaire used for quality of life assessment has been validated by Talebi et al. and the Cronbach-alpha for the CFQ-R was 0.65–0.91 for children and parents’ version, and ≥ 0.70 for the adult version, showing good internal consistency [43, 44]. The questionnaire forms can be accessed through the Supplementary file 3.

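### Exclusion items 9 and 10 describe conduct during treatment, so they exclude children already randomised; they should end treatment, not follow-up

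*Protocol article*

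**What the plan says.** Eligibility criteria {10} introduces Table 1 with the rule "Participants must meet all the eligibility criteria to be included". Two of its exclusion criteria concern behaviour once treatment is under way: item 9, "Improper patient cooperation during treatment sessions", and item 10, "Absence in 3 or more consecutive sessions".

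The other relevant statements are these:

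- **Allocation concealment {16b}:** the envelope is presented "After the initial evaluation of participants by the examiner", and the letter inside determines the treatment.
- **Interventions {11a}:** treatment starts 30 minutes after the first examination. The schedule is "The study will be conducted over 6 weeks, 3 times a week, with a total of 18 sessions", with the provision "Make-up sessions will be allowed if a session is missed".
- **Retention {18b}:** "In case of withdrawal of patients from the study, their data will be counted as drop-outs".
- **Outcome collection {18a}:** "Outcomes are assessed at two time points, at baseline, and after treatment sessions". Outcomes {12} puts the second assessment at six weeks.
- **Missing data {20c}:** multiple imputation.
- **Sample size {14}:** 11 per arm, raised by 30% to 15.
- **Blinding {17a}:** patients, outcome assessor and statistician are kept unaware of allocation. The treating therapist is not on that list.

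**The concern.** An eligibility criterion should be decidable before randomisation. A criterion that depends on what a child does in sessions acts afterwards, when the child already belongs to an arm. If meeting it takes the child out of the study, the comparison is no longer between the groups that were randomised.

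Two things are at stake. The first is information: a post-treatment measurement that could have been taken may be lost, in a trial of 30. The second is comparability. Item 9 is a judgement about conduct in sessions whose content differs by arm, and the therapist who delivers them is not among those kept unaware of allocation. Removals could therefore differ between arms.

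**Working it through.** **1. When can the items be judged?** The order in the text is initial evaluation, then envelope, then treatment ({16b}, {11a}). The only preparation described before treatment is teaching a home breathing technique and using it in place of sport ({11d}); no run-in sessions are described. Items 9 and 10 both refer to treatment sessions, so they can apply only to a randomised child.

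**2. How much absence meets item 10?** The plan's total reproduces: 6 weeks × 3 sessions = 18. Three consecutive sessions are 3/3 = 1 week, or 3/18 = 16.7% of the course. A child who attended the other 18 − 3 = 15 sessions could still meet the item.

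**3. What then happens to the child?** No section says directly. {18b} treats withdrawal as drop-out but does not name items 9 or 10. {18a} ties the second assessment to the treatment sessions, while {12} ties it to six weeks. {20c} plans imputation without saying who is still measured. If the post-treatment visit is missed, all outcomes from that visit are missing together. Imputation then has little to draw on beyond baseline values and cannot replace a measurement that could have been taken.

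**4. What does the plan already allow for?** 11 × 1.30 = 14.3, rounded up to 15 per arm, or 30 in total, as stated. The allowance is 15 − 11 = 4 per arm, or 8 children.

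**5. What does a lost outcome cost?** With equal arms and a fixed residual SD, the standard error of the difference is proportional to √(2/n). Relative to 15 per arm it grows by √(15/n):

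- One removal per arm (n = 14): √(15/14) = 1.035, about 3.5% wider.
- Four removals per arm (n = 11): √(15/11) = 1.168, about 17% wider. This is the planned base.

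The numbers removed are assumed. To illustrate their range, suppose a child misses a whole scheduled week with probability p, independently across weeks, and that missed sessions are not made up. The chance of at least one such week is 1 − (1 − p)^6:

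| Assumed p | Chance per child | Expected of 30 |
|---|---|---|
| 1% | 5.9% | 1.8 |
| 2% | 11.4% | 3.4 |
| 5% | 26.5% | 7.9 |

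No figure in the document supports any of these rates.

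**6. When would there be bias?** The planned ANCOVA compares arms, adjusting for baseline. Removals bias it only if they differ by arm or relate to outcome differently by arm. The text makes this possible but gives nothing from which to calculate a size.

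**The case against.** The strongest reply is that this is mostly a labelling fault: withdrawal rules have been placed in an exclusion table. No sentence says that such a child goes unmeasured or is left out of the analysis. Make-up sessions are allowed, so item 10 may rarely apply. Imputation may keep such a child in the analysis. The sample size already anticipates losses. Much of this stands, and it limits how far the point reaches.

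Three stronger readings are tempting, and the document does not support them.

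- **That an ill child will be dropped.** Item 10 has no exception for illness, and the make-up rule does not say whether a made-up session still counts as an absence. This is silence on operational detail. Section {31c} refers to a complete protocol, which may settle it.
- **That the trial loses its power.** One could fix the effect detectable with 80% power at 15 per arm (1.06 residual SDs) and report power falling to 66% at 11. The plan states no effect size, and 11 per arm is its own base, so this is not a loss against anything it promises. Nor can one say that the detectable effect moves from the plan's large band to its very large band. The value at 11 per arm, 1.259, is in residual-SD units, while Cohen's d is conventionally scaled by the raw SD. On that scale it is 1.259 × √(1 − r²), which is below 1.2 once the baseline correlation r exceeds √(1 − (1.2/1.259)²) ≈ 0.30.
- **That the comparison is biased.** That would need differential removal, which is possible but not shown.

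What the reply does not remove is the stated rule itself. The article makes conduct after randomisation a ground for exclusion, and that is not a detail left to another document.

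**Conclusion.** The point holds as a modest, avoidable design weakness. It is definite that items 9 and 10, as written, exclude children after randomisation, and that three consecutive absences, one week of six, meet item 10. It is an inference that such a child is then counted as a drop-out with no post-treatment outcome. It rests on reading the exclusion table together with the retention section, in the absence of any statement that excluded children are still assessed.

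The number of removals and the size of any bias cannot be derived. The drop-out allowance absorbs up to 4 losses per arm, so the sample size is not undermined. The reason to act is that losses created by this rule need not occur, and that assessing everyone removes one possible source of selection between arms. It is a change the sponsor could make; the trial does not depend on it.

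**What to change.** Take items 9 and 10 out of the exclusion list and restate them as a rule for stopping treatment, for example:

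> Improper cooperation, or absence from 3 or more consecutive sessions that are not made up, ends treatment only. Every randomised child is invited to the 6-week assessment and analysed in the allocated group; multiple imputation is used only for outcomes that are truly missing.

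Report treatment discontinuations by arm, with reasons. Keep the assessment at the six weeks given in Outcomes {12}; a timing that depended on the child's health would bring in a new problem.

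The cost is a short amendment through the ethics committee with a note on the registry, as Protocol amendments {25} provides, and one assessment for each child who would otherwise have been removed. The downside is that some children are analysed after fewer than 18 sessions, which slightly dilutes the effect of the full course. Recruitment had already begun at the date of this protocol version (Trial status), so the rule should also cover children already randomised whose 6-week visit can still be held.
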